## Abstract

**Background:**

Partial pancreatoduodenectomy (PD) is the indicated surgical procedure for a wide range of benign and malignant diseases of the pancreatic head and distal bile duct and offers the only potential cure for pancreatic head cancer. The current gold standard, open PD (OPD) performed via laparotomy, is associated with morbidity in around 40% of cases, even at specialised centres. Robotic PD (RPD) might offer a viable alternative to OPD and has been shown to be feasible. Encouraging perioperative results have been reported for RPD in a number of small, non-randomised studies. However, since those studies showed a considerable risk of bias, a thorough comparison of RPD with OPD is warranted.

**Methods:**

The EUROPA (EvalUation of RObotic partial PAncreatoduodenectomy) trial is designed as a randomised controlled unblinded exploratory surgical trial with two parallel study groups. A total of 80 patients scheduled for elective PD will be randomised after giving written informed consent. Patients with borderline or non-resectable carcinoma of the pancreatic head as defined by the National Comprehensive Cancer Network guidelines, distant metastases or an American Society of Anaesthesiologists (ASA) score > III will be excluded. The experimental intervention, RPD, will be compared with the control intervention, OPD. An intraoperative dropout of approximately eight patients per group is expected because they may receive another type of surgical procedure than planned. Overall, 64 patients need to be analysed. The primary endpoint of the trial is overall postoperative morbidity within 90 days after index operation, measured using the Comprehensive Complication Index (CCI). The secondary endpoints include the feasibility of recruitment and assessment of clinical, oncological and safety parameters and quality of life and cost-effectiveness.

**Discussion:**

The EUROPA trial is the first randomised controlled trial comparing RPD with OPD. Differences in postoperative morbidity will be evaluated to design a future multicentre confirmatory efficacy trial.

**Trial registration:**

German Clinical Trial Register DRKS00020407. Registered on 9 March 2020

## Background

By 2030, pancreatic cancer is expected to be the second leading cause of cancer-related deaths in the USA [1]. Each year, 610,000–915,000 quality-adjusted life-years are lost to pancreatic cancer in Europe [2], dramatically impairing the quality of life of patients and caregivers. Surgical resection offers the only chance of long-term survival. Partial pancreatoduodenectomy (PD) is the indicated surgical procedure for pancreatic head cancer and for a wide range of benign and other malignant diseases of the pancreas and distal bile duct.

Advances in surgical technique and perioperative care have decreased the perioperative mortality of pancreatic resection to below 5% at specialised high-volume centres. Perioperative morbidity, however, remains high, with rates around 40% [3]. Therefore, measures to reduce postoperative complications are urgently needed. Minimally invasive surgery has been shown to decrease postoperative morbidity in a wide range of surgical indications. Laparoscopic PD was introduced in 1994 [4] and robotic PD (RPD) in 2003 [5]. Several small, non-randomised and mostly retrospective and single-centre studies and case series have investigated RPD and compared it with open PD (OPD), with inconsistent results [6–14]. While the operating time was longer for RPD in most studies [6, 8, 9, 12, 15], comparable positive margin rates [11] and similar incidences of postoperative haemorrhage [10] were reported. While some studies found a higher number of harvested lymph nodes [9, 13], lower blood loss [7–9, 12, 13, 15] and fewer major complications for RPD [7], other studies reported the contrary, with higher margin positivity [6] and fewer harvested lymph nodes for RPD [6]. A meta-analysis of the limited data derived from a small number of mainly observational studies revealed the superiority of RPD for three efficacy outcomes: wound infection rate, margin positivity rate and length of hospital stay [16].

Overall, the study results show a positive trend in favour of the robotic approach. The evidence for equivalence or superiority of RPD is limited, however, due to the lack of a high-quality randomised controlled trial (RCT). Therefore, based on the current literature and in line with current IDEAL recommendations (stage 2b) [17, 18], an investigator-initiated exploratory RCT with standardised procedures, management and outcome definitions is needed before widespread adoption of RPD can be considered. Therefore, the EUROPA pilot trial will collect data on postoperative complications, safety, feasibility of recruitment and costs in order to design a large multicentre confirmatory clinical trial.

## Methods/design

### Trial rationale

This exploratory trial aims to compare the two different operative approaches, OPD and RPD, with regard to postoperative morbidity within 90 postoperative days (POD), measured using the Comprehensive Complication Index (CCI).

### Trial design

EUROPA is an investigator-initiated, exploratory, open-label RCT with two parallel study groups.

### Study registration, ethics and consent

The trial protocol was approved by the ethics committee of the University of Heidelberg (*Ethikkommission Medizinische Fakultät Heidelberg*; S-025/2020, 3 February 2020), and the trial was registered with the German Clinical Trial Register (DRKS), an approved primary registry in the WHO network (DRKS00020407, 9 March 2020; UTN U1111-1245-8931, 30 December 2019) before inclusion of the first patient. The trial will be conducted at the Department of General, Visceral and Transplantation Surgery, University Hospital Heidelberg, Germany, in accordance with the Good Clinical Practice (GCP) guidelines and the Declaration of Helsinki. More than 250 PDs are performed each year at the Department of General, Visceral and Transplantation Surgery, and it is certified as a centre of excellence for minimally invasive surgery by the German Society for General and Visceral Surgery (*Deutsche Gesellschaft für Allgemein- und Viszeralchirurgie*). Conservatively, five patients per month can be included in the trial. Thus, given the need to recruit 80 patients (see the “Sample size calculation” section), completion of recruitment is feasible within 18 months. The independent statistical analysis will be performed at the Institute of Medical Biometry and Informatics (IMBI) of the University of Heidelberg. All patient-related information is subject to medical confidentiality according to the European General Data Protection Regulation (*Datenschutzgrundverordnung*, DSGVO), the Federal Data Protection Act (*Bundesdatenschutzgesetz*) and the State Data Protection Act (*Landesdatenschutzgesetz*).

### Study population

All patients scheduled for elective PD will be screened consecutively for eligibility and will be informed about the EUROPA trial during a pretreatment visit or on the day of hospitalisation. Eligible for participation are all adult patients planned for elective PD for any indication who are judged suitable for both RPD and OPD by the treating pancreatic surgeon. Patients must provide written informed consent to the responsible study physician and must be able to understand the individual consequences of the clinical trial. The following exclusion criteria have been defined: (1) borderline or unresectable carcinoma of the pancreatic head as defined in the National Comprehensive Cancer Network guidelines [19], (2) distant metastases, (3) American Society of Anesthesiologists (ASA) score > 3, (4) participation in another interventional trial interfering with the intervention and outcome of this trial and (5) anticipated language problems or lack of compliance.

### Withdrawal criteria

Participants may withdraw from the trial at their own request at any time without giving reasons. If PD cannot be performed (e.g. because of technical irresectability or metastatic disease), the patient concerned will leave the trial early. The latter category will be included in the final report of the trial to ensure complete transparency.

### Interventions

In order to avoid the risk of learning-associated bias, only surgeons with sufficient proficiency will be allowed to perform the randomised interventions. Proficiency in the open group will be defined as having performed 40 or more OPDs, and in the robotic group, 40 or more RPDs. The requirement for a minimum of 40 RPDs is based on the results of research into learning curves for RPD [12, 20, 21].

In both groups, after exclusion of hepatic and peritoneal metastases, PD is performed by conventional resection and reconstruction with pancreato-jejunostomy, hepatico-jejunostomy and duodeno-jejunostomy/gastro-jejunostomy according to local standards [22].

Resection or preservation of the pylorus, the extent of lymphadenectomy, additional vascular resections, abdominal drain placement and abdominal wall closure at the end of the procedure are left to the surgeon’s discretion and will be documented in the electronic case report form (eCRF).

OPD, the current institutional standard procedure, will be performed as described before [22].

RPD was introduced at the Department of General, Visceral and Transplantation Surgery in November 2016, accompanied by a tutoring and proctoring programme. The procedure has been standardised and is performed as described in the Intuitive® surgical procedure guide, written by the members of our department [23]. Key components of the RPD procedure are defined and will be adhered to in this trial in order to provide consistent, reproducible results. The surgeon can decide to convert from RPD to OPD due to intraoperative circumstances or technical problems, and the reasons for conversion will be documented.

The same perioperative and postoperative standard operating procedures are in place for both interventions, and patients in both groups will be accommodated on the same wards to ensure standardised postoperative care.

### Assignment of intervention and randomisation

All consecutive patients will be screened, and reasons for non-inclusion must be documented in a screening list. In order to achieve comparable intervention groups for known and unknown risk factors, patients will be randomised before surgery using a centralised web-based tool (randomizer.at) provided by the Institute of Medical Informatics, Statistics and Documentation of the Medical University of Graz. Therefore, selection bias (biassed allocation to interventions) is minimised by sequence generation and allocation concealment. Randomisation will be conducted only by authorised trial personnel.

### Primary and secondary endpoints

The primary endpoint of the EUROPA trial is cumulative morbidity within 90 days after PD, assessed by means of the CCI. The CCI is based on the established Clavien–Dindo classification of postoperative complications, which has gained widespread acceptance [24]. The Clavien–Dindo classification grades postoperative complications according to their sequelae, ranging from grade I (any deviation from the normal postoperative course without the need for pharmacological treatment) to grade V (death). The CCI score ranges from 0 (no complication of any kind during the postoperative course) to 100 (death of patient). The CCI permits objective assessment of cumulative postoperative morbidity even in an unblinded study setting. The CCI was developed jointly by surgeons and patients and considers the patient’s perspective as well as objective parameters of surgical effectiveness [25]. It is validated for the pancreatic surgical population and a difference of 10 is regarded as clinically relevant [26].

The secondary endpoints cover important oncological, clinical, economic and patient-relevant outcomes (Table 1).

**Table 1 Tab1:** Definition of secondary endpoints

Secondary endpoint	Definition
General outcomes	
Feasibility of recruitment	Recruitment goal of *n* = 80 patients within 18 months.
Costs (€)	Procedure-related costs and all inpatient hospital costs up to POD 90.
Intraoperative outcomes	
Duration of surgery (min)	RPD: from the start of positioning of the robot to the end of skin closure. OPD: from the beginning of skin incision to the end of skin closure.
Blood loss (ml)	As recorded in the anaesthesiology report.
Serious intraoperative complications	Any untoward medical/surgical occurrence that results in death, is life-threatening, requires prolongation of existing hospitalisation or results in persistent or significant disability/incapacity. Intraoperative in this context is defined as from the beginning of anaesthesia until the end of skin closure.
Conversion rate (%)	Conversion rate from robotic to open surgery.
Surgeon’s mental workload/stress	Self-evaluation according to the National Aeronautics and Space Administration Task Load Index [27] at the end of surgery.
Oncological outcomes	
Rate of complete margin clearance in patients with malignant tumours	a. Microscopically complete margin clearance > 0.1 cm margin clearance, R0 (CRM−). b. Microscopic margin clearance ≤ 0.1 cm, R0 (CRM+). c. Microscopic margin involvement (R1) resections according to the 8th edition of the UICC TNM classification.
Lymph nodes in patients with malignant tumours	a. Number of lymph nodes resected. b. Number of tumour-positive lymph nodes.
Postoperative outcomes	
Mortality (%)	From the day of surgery until postoperative day 90.
Quality of recovery	Measured via the quality of recovery questionnaire QoR-15 [28], assessed at baseline and on POD 4.
Time to functional recovery (days)	Up to postoperative day 90; defined as: independently mobile at the preoperative level, sufficient pain control with oral medication alone, ability to maintain sufficient (i.e. > 50%) daily required caloric intake by mouth, no intravenous fluid administration and no signs of infection [29].
Total length of intensive care unit stay (days)	From the day of index operation up to postoperative day 90.
Length of hospital stay (days)	From the day of index operation up to the day of discharge.
Rate of superficial and deep surgical site infections (SSIs)	As defined by the Centres of Disease Control and Prevention (CDC) within 30 days [30]. Organ-space SSIs are excluded from this measurement as they are independent of surgical access, but rather depend on the underlying surgery. Consequently, organ-space SSIs will be recorded in the overall complication rate if applicable.
Pancreas-specific complications	Rate and severity within 90 days of: a. Postoperative pancreatic fistula as defined by the ISGPS [31]. b. Postpancreatectomy haemorrhage as defined by the ISGPS [32]. c. Delayed gastric emptying as defined by the ISGPS [33]. d. Biliary leak as defined by the ISGLS [34]. e. Chyle leak/lymphatic fistula as defined by the ISGPS [35].
Non-surgical re-interventions	Number of non-surgical re-interventions within 90 days after PD (e.g. image-guided drain placement, angiography with stenting/other interventions, endoscopy).
Re-operations	Number of re-operations within 90 days after PD.
Hospital re-admissions	Number of hospital re-admissions within 90 days after PD.
Pain	Pain scores at rest and during movement according to the Numeric Rating Scale (NRS) on POD 2 and 4.
Health-related quality of life (HRQoL)	Measured by the SF-36 at baseline, 30 and 90 days after index operation [36].

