#### Analysis variables and statistical methods

The primary endpoint is the CCI within 90 days after the intervention. As a primary result, the 95% CI for the difference in the means between the two groups will be reported. Since the CCI is approximately normally distributed [25], the 95% CI can be computed by means of the normal distribution. Further descriptive measures are reported in terms of mean and standard deviation.

Data analysis will be based on three analysis sets. The intention-to-treat (ITT) set comprises all patients in the group to which they were randomised (converted patients remain in the RPD group) and serves as the primary analysis set. Patients that receive an operation other than PD or total pancreatectomy (explorative laparotomy, diagnostic laparoscopy, etc.) are excluded from further analysis and proceed directly to the end-of-study visit (V8). The per-protocol (PP) set consists of all patients treated per protocol without major protocol violation and without conversions. No missing data will be imputed in the PP set. In addition, the as-treated set will be analysed, which considers the patients in the group in which they were finally treated (i.e. converted patients in the OPD group). There is no evidence that the converted patients will have a higher postoperative CCI than those patients randomised to and remaining in the OPD group. Therefore, and due to the exploratory character of this trial, the as-treated set is an important complement to the ITT and PP sets in this trial.

The primary endpoint is expected to be missing for a small number of patients, since it is objective and short term. In these cases, the primary endpoint is imputed using mean imputation based on the treatment group. As sensitivity analyses, worst-case and best-case scenarios are investigated. Missing values of the primary endpoint will be imputed using the lowest and the highest value of the corresponding treatment group.

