The secondary endpoints are described as mean values along with standard deviations, median values, quartiles, minimum and maximum for continuous endpoints, and relative and absolute frequencies for categorical endpoints, stratified for treatment groups. Effect sizes (mean difference for continuous data, Hodges–Lehman estimator for scores and risk difference for binary data) including 95% CIs will be reported. The safety analysis includes calculation of frequencies and rates of both minor (Clavien–Dindo class I and II) and major complications (Clavien–Dindo class III to V) together with 95% CIs. Statistical methods will be used to assess the quality of data and the homogeneity of the intervention groups.

Details of statistical analyses as well as the handling of potential data problems will be defined in a statistical analysis plan (SAP) prior to database closure.

All analyses are exploratory, having only descriptive character, and will be conducted using SAS version 9.4 or higher.

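### Duration of surgery starts at robot positioning in one arm and at skin incision in the other, so the planned mean difference is not a like-for-like operating time

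*Protocol article*

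**What the plan says.** The protocol article, Table 1 (under Primary and secondary endpoints), lists duration of surgery in minutes among the intraoperative outcomes and gives it two definitions: "RPD: from the start of positioning of the robot to the end of skin closure. OPD: from the beginning of skin incision", the open-arm clock likewise stopping at the end of skin closure. The end event is shared and the start event is not. The article gives no reason for the difference.

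Under Analysis variables and statistical methods, the rule for secondary endpoints is "Effect sizes (mean difference for continuous data, Hodges–Lehman estimator for scores and risk difference for binary data) including 95% CIs will be reported". Duration is continuous, so it falls under the mean difference.

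The same section sets out how conversions are handled. In the intention-to-treat (ITT) set "converted patients remain in the RPD group", the per-protocol (PP) set leaves conversions out, and the as-treated set places "converted patients in the OPD group".

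For serious intraoperative complications, Table 1 uses a window that is the same in both arms, running from the beginning of anaesthesia to the end of skin closure.

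**The concern.** A between-arm difference in duration can be read as an effect of the operative approach only if both arms are timed over the same span. Here the robotic clock starts at an event that does not exist in the open arm. The reported difference therefore combines two things: how much longer or shorter the operation takes, and how far robot positioning lies from skin incision.

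Readers are likely to look at this comparison. The Background notes that operating time was longer for RPD in most of the cited studies, and the Discussion says the pilot should help to plan a confirmatory trial, mentioning theatre restrictions and capacity. A difference that depends partly on where the clock starts is a weak basis for either use.

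**Working it through.** **Inputs from the protocol article.** Start and end events by arm (Table 1); mean difference with 95% CI for continuous endpoints, and the analysis sets (Analysis variables and statistical methods); 32 analysed patients per group (Sample size calculation). The article states no expected value, standard deviation (SD) or precision for duration of surgery, so there is no figure of the plan to reproduce.

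**Step 1: what the planned contrast estimates.** Let S be the start of robot positioning, I the skin incision and C the end of skin closure.

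Planned difference = E[C − S | RPD] − E[C − I | OPD]

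Since C − S = (C − I) + (I − S), this equals

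(E[C − I | RPD] − E[C − I | OPD]) + E[I − S | RPD].

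The bracket is the skin-to-skin difference. The last term is the mean interval from robot positioning to incision. It occurs in the RPD arm only and does not depend on sample size.

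**Step 2: sign of the extra term.** The article does not say whether positioning begins before or after incision.
- If before, I − S is positive, and RPD time includes set-up that OPD time does not.
- If after, I − S is negative, and RPD time omits an opening phase that OPD time includes. The Interventions section says "In both groups, after exclusion of hepatic and peritoneal metastases, PD is performed by conventional resection and reconstruction", so if positioning followed that exploration, a step common to both arms would be timed in only one.

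**Step 3: scale, on assumed values only.** The 95% CI half-width for a difference of means, with equal SD in both arms, is 1.96 × SD × √(2/32) = 1.96 × SD × 0.25.
- SD 60 min: 29.4 min
- SD 90 min: 44.1 min
- SD 120 min: 58.8 min

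Suppose the true skin-to-skin difference is 0. The expected CI is then centred on the offset I − S:

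| Assumed offset (min) | SD 60 | SD 90 | SD 120 |
|---|---|---|---|
| −40 | −69.4 to −10.6 | −84.1 to 4.1 | −98.8 to 18.8 |
| −20 | −49.4 to 9.4 | −64.1 to 24.1 | −78.8 to 38.8 |
| +20 | −9.4 to 49.4 | −24.1 to 64.1 | −38.8 to 78.8 |
| +40 | 10.6 to 69.4 | −4.1 to 84.1 | −18.8 to 98.8 |

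Only the most extreme combination (40 min either way with SD 60) excludes zero through the definition alone. In the other cells the interval is displaced but still covers zero.

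**Step 4: conversions, by analysis set.**
- ITT: converted patients stay in the RPD group and keep its start event, so each group has one clock.
- PP: conversions are excluded, so each group has one clock.
- As-treated: converted patients move to the OPD group. Table 1 does not say which start event then applies. If the robotic start is kept, that group contains both clocks.

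**The case against.** The strongest reply is that skin-to-skin time is never declared to be the target. Robot set-up is a real part of what RPD takes up in theatre, the Discussion names organisational burden as something the pilot should inform, and the definitions are printed openly by arm. On that view the asymmetry is a choice and not an error. It is fair that counting set-up may be deliberate, and that a skin-to-skin measure alone would leave out any set-up done before incision. But a burden measure also needs the same start in both arms, because an open operation has preparation before incision too. As defined, the endpoint measures neither skin-to-skin time nor total burden in both arms.

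It can also be said that the eCRF and the statistical analysis plan, neither shown here, may record both time stamps or add an analysis on a common clock. That is possible and would make the fix cheaper. It does not alter the definition that the article fixes.

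Three stronger readings are tempting but not supported:
- **RPD is made to look slower.** The documents do not place robot positioning before or after incision, so no direction can be claimed.
- **Conversions mix the clocks throughout.** This can happen only in the as-treated set (Step 4).
- **The cost endpoint inherits the problem.** Table 1 defines costs as procedure-related and inpatient hospital costs up to day 90 and does not say that they are derived from this duration.

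**Conclusion.** The point holds in a limited form. The planned RPD–OPD difference in duration is the skin-to-skin difference plus an RPD-only interval of unknown sign and size, so it should not be read as a like-for-like operating time. This follows from the stated definitions and needs no assumption. How much it matters does rest on assumptions: the offsets (−40 to +40 min) and SDs (60 to 120 min) above are illustrative and have no source in the documents.

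Severity is modest. Duration is one of many secondary endpoints, the article describes all analyses as exploratory and descriptive, and the primary endpoint, the Comprehensive Complication Index, is untouched.

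**What to change.** In Table 1, define duration of surgery identically in both arms, from first skin incision to end of skin closure, and use that for the mean difference and its CI. This also settles the as-treated set, since a converted patient then has the same clock in either group.

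Report robot positioning or set-up time as a separate, RPD-only descriptive item, and state whether it falls before or after incision. If total theatre burden is of interest, add a second measure with a common start, such as beginning of anaesthesia to end of skin closure, the window Table 1 already uses for serious intraoperative complications.

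The cost is a reworded table row and, if the eCRF does not already hold it, one extra time stamp (skin incision in RPD). Whether that time can be recovered for patients already operated on is not something the documents show. The small downside is that skin-to-skin time omits any set-up done before incision, which is why set-up time should be reported alongside it.
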